## Background

Obstructive sleep apnea syndrome (OSA) is a chronic sleep disorder characterized by repeated episodes of upper airway collapse during sleep. This leads to arterial hypoxemia and sleep disruption and causes daytime sleepiness and several associated dysfunctions, including cardiovascular, respiratory, metabolic, inflammatory, cognitive, and behavioral disorders.^1^ OSA is a relevant public health issue, with epidemiological studies showing a prevalence of 10% in middle-aged men and 3% in middle-aged women.^2^ Moreover, OSA has been associated with the development of cardiovascular events^3, 4^ and resistant hypertension,^5^ has a negative impact on quality of life,^6^ and has even been shown to have a causative role in traffic accidents.^7^ The application of continuous positive airway pressure (CPAP) is a highly effective treatment for OSA that can improve symptoms and quality of life, decrease traffic accidents and potentially lessen cardiovascular morbidity.^8, 9^ Furthermore, CPAP is cost-effective.^10^ However, only approximately 10% of individuals with OSA are diagnosed and treated. This scarcity in diagnosis has direct public health consequences due to the above-mentioned health implications and the high economic costs associated with untreated OSA.

Currently, the diagnosis and management of OSA are performed in highly specialized hospital-based sleep units (SUs), where full sleep studies (polysomnography (PSG)) or respiratory poligraphy (RP) can be conducted. However, this management approach has proven to be insufficient in identifying most OSA cases in the population, in addition to being cost-ineffective and generating long waiting lists.^11^ Given that OSA is a common chronic disorder, we believe that all levels of a healthcare system, especially primary care (PC), should be included in its management.^12–14^ The first trials assessing the management of OSA at the PC level reported satisfactory results.^15–19^ Moreover, our group showed that CPAP compliance did not differ between the PC and SU setting and was more cost-effective in the PC setting.^19^ However, in the above studies, although OSA management occurred at the PC level, diagnosis had always occurred in a SU. Therefore, in the current study, we aimed to determine the efficacy and cost-effectiveness of implementing a program for the diagnosis and management of OSA that can be conducted by PC personnel, and we compared these outcomes to those generated using the standard diagnosis and management protocols that are practiced in SUs.

### AIMS

The main objectives of the GESAP study are to assess the efficacies of PC and SU programs for OSA management. These assessments will be made using the Epworth sleepiness scale (ESS) before and for 6 months after initiating the program to assess its cost-effectiveness based on both ESS and quality of life (EuroQol-5D). Secondary objectives include assessments of patient satisfaction, treatment compliance, and the number, severity, and evolution of the treatment’s side effects.

## Methods

### Design

This is an open-label, parallel, prospective, randomized controlled trial. Figure 1 shows the study flow diagram. Patients will be consecutively included while attending visits with PC physicians due to suspected OSA or resistant hypertension. The included patients will be randomized by PC personnel to either PC or SU management in a 1:1 ratio. The patients randomized to SU management will be forwarded to the SU. Finally, after achieving an appropriate diagnosis and completing a 6-month course of follow-up, outcome evaluation and cost-effectiveness analysis will be performed. This research was approved by the Ethical Committee for Clinical Research of the Hospital Arnau de Vilanova—Santa Maria (Lleida, Spain), and the trial has been registered at ClinicalTrials.gov Id: NCT02234765.

**Fig. 1 Fig1:**
[figure not shown]
Study flow diagram

### Subjects

The following inclusion criteria will be applied (Table 1): patients over 18 years of age visiting a PC unit in the region of Lleida, Spain, because of suspected OSA, based on the presence of chronic snoring, partner-objectified apnea and/or excessive daytime sleepiness or because of resistant hypertension (Alcarràs, Bordeta-Magraners, Borges Blanques, Cappont, Ciutat Jardí, Primer de Maig, El Pla d’Urgell, Ponts, Tàrrega, Rambla Ferran and, Balàfia-Pardinyes-Secà). All patients will be required to provide written informed consent.

**Table 1 Tab1:** Inclusion/exclusion criteria

Inclusion criteria	Exclusion criteria
Men and women age >18 years	Pulmonary illness
Patient suspected to have OSA or resistant hypertension	Advanced heart failure (NYHA III or IV)
	Associated advanced pathology (including any active neoplasm or tumor)
	Psychiatric disorder
	Restless legs syndrome
	Pregnancy
	Another dyssomnia or parasomnia
	Previous treatment with CPAP

### Randomization and intervention

Randomization will be performed using an automated password-protected system, stratified by center. Each enrolled patient will be allocated in a 1:1 ratio to either the SU or PC arm. A total of 280 patients will be randomized (140:140). The patients randomized to the SU arm will be forwarded to the SU of Hospital Arnau de Vilanova—Santa Maria. In the SU, the patients will be diagnosed using PSG or RP as per usual clinical practice. Excessive daytime sleepiness will be measured using the validated Spanish version of the ESS.^20^ Patient follow-up and monitoring will be performed by SU personnel. In the PC arm, PC physicians will administer the ESS and request sleep testing from an external enterprise that supplies home respiratory therapies in the study area (the personnel of this enterprise have adequate training and expertise). Sleep tests will be performed using RP devices that meet the requirements for producing level III evidence proposed by the American Sleep Disorders Association. A full report will then be forwarded to the PC physician, who will choose an appropriate therapeutic option and perform monitoring and follow-up. The PC physicians will receive training from SU personnel before the study starts.

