### Sample size calculation

According to the literature, a calculation will be performed to support a non-inferiority analysis with ESS as the main study variable. A loss of 30% will be assumed,^23^ as well as an alpha error = 0.05, a beta error = 0.2, a non-inferiority limit of −2, and a common standard deviation for the two groups of ±5.9 for the principal variable.^24^

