### Statistical analysis

Efficacy assessment will include per protocol analysis, excluding subjects who do not complete the follow-up. Adjusted analysis of covariance will be used to compare changes in ESS before and after the intervention in each study arm (non-inferiority margin = −2 points). *χ*
^2^ tests and *t*-tests (or non-parametric equivalents) will be used to compare quality of life (EuroQol-5D) and adherence to treatment in the 2 study arms as appropriate. Stratified analyses by CPAP treatment will be performed.

Cost-effectiveness assessment will include an intention-to-treat analysis to assess the total costs for each arm based on treatment effectiveness (ESS and EuroQol-5D). This will be performed using Bayesian cost-effectiveness techniques. The cost-effectiveness ratio of each treatment, the incremental cost-effectiveness ratio, the cost-effectiveness plane, the net benefit (NB) of each treatment, the incremental NB, and the cost-effectiveness acceptability curve will be considered.

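### With the stated 30% loss, 140 patients per arm leave 98 for the efficacy analysis and about 77% power for the unadjusted comparison, not the stated 80%

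*Protocol article*

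**What the plan says.** Three sections of the protocol article bear on this point.

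- **Randomization and intervention** gives the total: "A total of 280 patients will be randomized (140:140".
- **Sample size calculation** says that "a calculation will be performed to support a non-inferiority analysis with ESS as the main study variable". It lists "an alpha error = 0.05, a beta error = 0.2, a non-inferiority limit of −2". The SD is 5.9 in both arms. On attrition it states: "A loss of 30% will be assumed". It shows neither the resulting number nor the step that allows for loss, and it does not say whether alpha is one-sided.
- **Statistical analysis** makes the efficacy assessment per protocol, "excluding subjects who do not complete the follow-up". It compares the change in ESS between arms by adjusted analysis of covariance, with the same margin ("non-inferiority margin = −2 points").

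**The concern.** The inputs and the total are both published, so they can be checked against each other. A 30% loss leaves 70% of those randomised. The number randomised must therefore be the evaluable number divided by 0.7. Multiplying by 1.3 is a common slip, and it protects only against a smaller loss. Because patients without complete follow-up do not enter the efficacy analysis, any such shortfall falls directly on the non-inferiority test.

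What is at stake is the stated type II error. If the trial fails to exclude a 2-point deficit, readers will weigh that result against a power of 80%. That figure should be one that the design has under its own assumptions.

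**Working it through.** **Inputs.** From Sample size calculation: SD σ = 5.9, margin Δ = 2, alpha 0.05, beta 0.2, loss 30%. From Randomization and intervention: 140 per arm. From Statistical analysis: completers only. Assumed here because the article does not say: alpha is one-sided, the true difference is 0, and 5.9 is the SD of the quantity analysed.

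**1. Evaluable patients needed per arm.**

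n = 2(z₀.₉₅ + z₀.₈₀)² σ² / Δ² = 2(1.645 + 0.842)² × 5.9² / 2² = 107.6, so 108.

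**2. Reproducing the stated 140.**

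- Multiplying: 107.6 × 1.3 = 139.9, so 140 per arm and 280 in total. This matches. If 107.6 is rounded up first, 108 × 1.3 = 140.4, so 141 per arm and 282 in total.
- Dividing: 108 / 0.7 = 154.3, so 155 per arm and 310 in total. This does not match.

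**3. The allowance that 140 contains.** 140 − 108 = 32 patients per arm, which is 32/140 = 22.9% of those randomised. A 30% loss would be 0.30 × 140 = 42 per arm.

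**4. Completers after a 30% loss.** 140 × 0.7 = 98 per arm, 10 short of 108.

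**5. Power with 98 per arm, unadjusted.**

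- SE = 5.9 × √(2/98) = 0.843.
- Power = Φ(2/0.843 − 1.645) = Φ(0.728) = 76.7%. The noncentral t gives 76.4%.
- The type II error is about 23% instead of 20%.

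**6. Largest loss at which 140 per arm keeps 80%.** 1 − 107.6/140 = 23.1%.

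**7. Sensitivity to the sidedness of alpha.** With one-sided 0.025 (the lower limit of a two-sided 95% CI):

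- The evaluable number is 136.6, so 137 per arm.
- 137 / 0.7 gives 196 per arm (392 in total), and 137 × 1.3 gives 179 per arm (358 in total). Neither is 280.
- With no allowance for loss the total would be 274. That is near 280 but ignores the stated 30%.
- Power with 98 per arm would be Φ(2/0.843 − 1.960) = 66.0%.

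**8. What the ANCOVA could recover.** To reach 80% with 98 per arm, the variance must fall to 98/107.6 = 0.911 of 5.9².

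- If 5.9 is the SD of ESS at one time point, the residual variance is (1 − r²)σ², where r is the correlation between baseline and follow-up. Then 1 − r² = 0.911 gives r of about 0.3. At r = 0.3 the power is 80.0%.
- If 5.9 is the SD of the change, and baseline and follow-up variances are equal, the ratio of ANCOVA to change-score variance is (1 + r)/2. This is at most 0.911 for any r up to about 0.82.

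**The case against.** The strongest reply is that the planned analysis is not the unadjusted comparison that the calculation describes. Adjustment for baseline ESS reduces the residual variance. As step 8 shows, a modest correlation would bring 98 per arm back to 80% at one-sided 0.05. This stands as a qualification: the documents do not show that the ANCOVA as planned will have less than 80% power. It does not remove the error, because the sample size section gives no correlation, does not say which SD 5.9 is, and claims no gain from adjustment. On the figures printed, 80% is not reached.

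The reply can add that no multiplication by 1.3 is printed. That is true. The close match makes it a strong inference, but the shortfall does not depend on it: 140 × 0.7 is 98 however 140 was chosen.

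It is also fair to say that 3 points of power is little. No type I error, margin or analysis is affected.

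A reader might go further and infer that the trial has only 66% power, because alpha of 0.05 could mean a two-sided 95% confidence interval. The article does not support that as a defect. It specifies no such interval, and that reading does not reproduce 280 once the loss is allowed for. A condensed article may also leave the confidence level to the full protocol or analysis plan. The 66% is a conditional sensitivity figure only.

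**Conclusion.** The published inputs and the published total do not agree. At the assumed 30% loss, 280 randomised patients give 98 evaluable per arm against 108 needed, and about 77% power for the unadjusted comparison. The beta of 0.2 holds only if loss stays at or below about 23%. These figures rest on a one-sided alpha of 0.05, a true difference of 0, and an SD of 5.9 for the quantity analysed.

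The point should be fixed, but it is a modest misstatement of power and not a flaw that undermines the design. A reader might conclude that the trial cannot reach 80% at all. That does not follow, because the adjusted analysis may recover the difference. The plan simply does not give the figure that would show it.

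**What to change.** Keep 280 and correct the statement in Sample size calculation. Either of these would do:

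- State that 98 evaluable patients per arm after a 30% loss give about 77% power at one-sided alpha 0.05, with a true difference of 0 and no adjustment, and that 80% holds for losses up to about 23%.
- If the gain from ANCOVA is relied on, say whether 5.9 is a single-time-point SD or the SD of change, and give the baseline correlation or residual SD that restores 80% with 98 per arm.

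In both cases, print the sidedness of alpha next to the power so that the figure can be read without guessing.

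The cost is wording only. No extra patients are needed, and the margin and the analysis stay as they are. Under the first option the stated power becomes about 3 points less favourable.

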### Study variables and data collection

The following variables will be collected at recruitment and at the 6-month follow-up: (i) clinical variables, including age, sex, daytime sleepiness (ESS), blood pressure, and drug use habits; (ii) anthropometric variables, including weight, height, BMI, and neck, waist and hip circumferences; (iii) comorbidities, including depression, anxiety, hypertension, heart, neurological, or respiratory diseases, non-active neoplasm, diabetes, and dyslipidemia; (iv) PSG or RP variables, including recording time, AHI, saturation <90% (CT90); and (v) quality of life (EuroQol-5D) and work or traffic accidents. Additionally, the compliance of patients undergoing CPAP treatment will be determined by dividing the number of hours of use (obtained from the internal clock of the CPAP device) by the number of days of treatment; adequate compliance will be defined as CPAP use ≥4 h/day. The final follow-up visit will also include an visual analog questionnaire on satisfaction about the received care in addition to an estimation of the overall direct costs of the treatment based on (i) sleep test costs (RP, PSG, and titration by automatic CPAP); (ii) CPAP treatment costs; (iii) patients’ travel costs; and (iv) healthcare costs 6 months before and after randomization, including number of PC and SU consultations and number and duration of emergency or day hospital admissions. Hospital and PC costs will be assessed using prices provided by the Catalan Institute of Health.^22^

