## Discussion

We believe that satisfactory management of the diagnosis and treatment of patients with suspected OSA can be obtained in the PC setting by performing actions at various levels, including the interactive training of PC teams, the sharing of electronic medical records between PC units and SUs, and the use of current technology. We expect that the included patients will achieve a comparable level of clinical response, satisfaction, treatment compliance, and complication avoidance in both the PC and SU settings. In addition, we expect that PC management will be more cost-effective than the standard SU management. Overall, we believe that this project could establish a new paradigm for the management of a common condition that involves different levels of care as well as new technologies, and could demonstrate the ability to cost-effectively manage this chronic disease in the PC setting.

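### The listed cost components leave out the training of PC physicians, which understates PC cost by an unknown amount, and the role of pre-randomisation costs is not fixed

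*Protocol article*

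**What the plan says.** All of this is in the protocol article.

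- **Randomization and intervention:** "The PC physicians will receive training from SU personnel before the study starts". It describes no matching training for the SU arm. It also fixes 140 patients per arm.
- **Discussion:** the actions expected to make PC management work are given as "including the interactive training of PC teams, the sharing of electronic medical records between PC units and SUs, and the use of current technology". The authors also say they expect PC to be the more cost-effective setting.
- **Study variables and data collection:** at the final visit there is to be an "estimation of the overall direct costs of the treatment based on (i) sleep test costs (RP, PSG, and titration by automatic CPAP"), followed by "ii) CPAP treatment costs; (iii) patients’ travel costs". The fourth and last component is given as "healthcare costs 6 months before and after randomization, including number of PC and SU consultations and number and duration of emergency or day hospital admissions". Valuation uses prices from the Catalan Institute of Health.
- **Statistical analysis:** the cost-effectiveness assessment is by intention to treat, compares total costs per arm and uses Bayesian methods. It gives the costs from before randomisation no separate role.

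**The concern.** Cost-effectiveness is a main objective, and what is being evaluated is a programme run by PC personnel. If training is part of the programme, it is part of what the programme costs. A cost list that picks up tests, CPAP, travel and health service use, but not the training, makes PC look cheaper than it is. The error runs one way, towards the conclusion the authors anticipate.

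The second matter is smaller. Health service use before randomisation cannot be a consequence of the allocated arm, yet item (iv) puts it under the heading of treatment cost. If an analyst took the list literally and added the two periods together, the cost difference would carry variation that has nothing to do with the intervention. The intervals for incremental cost and incremental net benefit would be wider than they need be.

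**Working it through.** The article states no cost figure, so there is none to reproduce. The only plan figure used below is 140 patients per arm. Every cost, SD ratio and correlation is an assumption shown as a range.

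**1. Can the listed components capture training?**

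| Component | Could it contain training? |
|---|---|
| (i) sleep tests and titration | No |
| (ii) CPAP treatment | No |
| (iii) patients' travel | No |
| (iv) healthcare costs, including consultations and emergency or day hospital admissions | No: it is patients' use of services, whereas training is staff time spent before the study starts |

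Training uses both SU time (trainers) and PC time (trainees), and it serves the PC arm.

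**2. Size of the omission.** Let T be total training cost. If it is charged wholly to the trial, the amount missing per PC patient is T/140.

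| Assumed T (currency units) | T/140 |
|---|---|
| 2,000 | 14 |
| 5,000 | 36 |
| 10,000 | 71 |
| 20,000 | 143 |

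If the training serves m times as many patients over its useful life, the figure is T/(140m). With an assumed m = 5 the range falls to 2,000/700 = 3 up to 20,000/700 = 29.

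**3. Pre-randomisation cost: bias.** Randomisation makes its expectation equal in the two arms, so its expected contribution to the difference in mean cost is zero, whether or not it is added.

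**4. Pre-randomisation cost: precision.** Set the variance of post-randomisation cost to 1. Let k be the ratio of pre- to post-randomisation SD, and r the correlation between the two. The variance of the arm difference is then proportional to:

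- post-randomisation cost only: 1
- pre and post summed: 1 + k² + 2rk
- post-randomisation cost adjusted for pre: 1 − r²

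Square roots give the standard error relative to post-randomisation cost alone:

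| r | Summed, k = 1 | Summed, k = 0.5 | Adjusted (any k) |
|---|---|---|---|
| 0.3 | √2.60 = 1.61 | √1.55 = 1.24 | √0.91 = 0.95 |
| 0.5 | √3.00 = 1.73 | √1.75 = 1.32 | √0.75 = 0.87 |
| 0.7 | √3.40 = 1.84 | √1.95 = 1.40 | √0.51 = 0.71 |

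At r = 0 the summed ratios are √2 = 1.41 (k = 1) and √1.25 = 1.12 (k = 0.5), and the adjusted ratio is 1.00. Summing therefore costs precision throughout this range, while adjustment leaves it unchanged or improves it.

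**The case against.** **On training.** The costs are described as an estimate based on four headings, in a condensed article, and a full protocol might treat set-up cost elsewhere. SU set-up and staff training are not itemised either, and the Catalan Institute of Health prices may absorb overheads of that kind in ways that cannot be seen here. Whether a one-off cost incurred before the study belongs in a 6-month per-patient comparison is also a choice of costing perspective, and spreading it over future patients shrinks it.

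Much of this stands as a limit on size and certainty. It does not remove the point. The article does enumerate its components, it names training as a means by which PC management works, and training specific to the PC programme falls under none of the four headings.

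**On pre-randomisation costs.** A reader might infer that the plan adds the two periods and that this distorts the comparison. The documents do not support that. The list sits in a data collection section, and nothing there or under Statistical analysis says the periods are summed. Collecting "healthcare costs 6 months before and after randomization" suits a baseline adjustment or a before-after change at least as well. Even a sum would cause no bias. Equal SDs may also be too pessimistic: only item (iv) has a component from before randomisation, and prior CPAP treatment is an exclusion, so post-randomisation cost has sources of variation that the earlier period lacks. The k = 0.5 column may be nearer the truth. Finally, the loss of precision should be judged against post-randomisation cost alone. Measuring it against baseline-adjusted cost would add in the gain from an optional adjustment.

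**Conclusion.** The training point holds in direction. As listed, the cost components understate PC cost, and the understatement favours the expected conclusion. Its size is not computable from the documents. The 14 to 143 per patient rests wholly on an assumed T of 2,000 to 20,000 charged to 140 patients, and it falls with amortisation. A reader might go on to infer that the cost-effectiveness result would change. Nothing supports that, because no arm cost, expected saving or willingness-to-pay threshold is given to compare it with.

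The pre-randomisation point is one of unclear wording. It concerns precision, not bias, and it matters only if the periods are summed. In that case the standard error would be about 1.6 to 1.8 times that of post-randomisation cost at equal SDs and r of 0.3 to 0.7, and about 1.2 to 1.4 times at an SD ratio of 0.5. It is worth settling because data already being collected can serve as a covariate.

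**What to change.** - **Training.** Record trainer and trainee hours, value them, and charge them to the PC arm. State the amortisation: how many patients or years the cost is spread over. Report the incremental cost-effectiveness ratio, the net benefit and the acceptability curve with and without this cost.
- **Pre-randomisation cost.** Define total cost as cost incurred after randomisation. State that healthcare cost from the preceding 6 months enters the cost model as a baseline covariate and is not part of the total.

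The price is a one-off record of hours, a few sentences in the analysis text and one extra set of cost results. PC cost becomes slightly less favourable. Patients, visits and sample size are unaffected.
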